### Health economic analysis

A cost analysis will be performed from a hospital perspective to compare the cost per patient in each treatment group. Data relating to patients’ primary hospital admission is collected prospectively until primary hospital discharge (including but not limited to their length of stay on a ward and in the intensive care unit). Data relating to readmissions, accident and emergency attendances and outpatient attendances is collected at 90 days. Unit costs will be obtained from public sources, e.g. Department of Health reference costs. Differences in costs between groups will be estimated using regression methods adjusted for baseline and other covariates where appropriate.

## Discussion

TXA is effective at reducing blood loss in elective joint arthroplasty. TRAC-24 extends administration of TXA to primary THA and TKA patients up to 24 h post-operatively with the aim of further reducing blood loss. The coagulation pathway for TXA is a system with a tightly controlled balance and theoretically TXA could act as a pro-coagulant and produce VTE. To date, there is no evidence to suggest it does. A Cochrane review in 2011 concluded that TXA did not increase the risk of death, myocardial infarction, cerebrovascular accident, deep vein thrombosis, pulmonary embolism or renal impairment [31]. In 2014, Poeran retrospectively analysed outcome data on 872,416 TKA or THA patients and found no increase in thromboembolic events nor renal impairment with TXA use [32]. However, all published randomised controlled trials to date have excluded patients with previous thromboembolic disease. The data are, thus, criticised for not reflecting a true safety profile. TRAC-24 is novel in that such patients are not excluded and thus, it is intended that this study will assist in defining the safety profile of TXA in primary joint arthroplasty for patients with a history of thromboembolic disease.

Since TRAC-24 commenced, there have been several challenges to overcome. Firstly, recruitment has taken longer than expected. This is primarily because of a reduction in the number of primary THA and TKA operations performed at the study site since the study was planned. In addition, there was a delay in starting the study and we have also found seasonal changes in recruitment due to, for example, a winter bed crisis that reduced the number of elective procedures performed. Additional funding was secured to enable the study to continue. In addition, there was difficulty in collecting some of the data for the exploratory outcomes at the 90-day time point. The protocol stated that participants would be contacted via telephone for this information; however, the information they provided was not always complete and participants did not always answer their telephone. To avoid important safety data being missing for the study, an amendment was approved allowing us to use the Northern Ireland Electronic Care Record to collect this data for all prospective participants and for all participants who had already been recruited, if their data could not be obtained using the original protocol.

Originally, this study had been designed with three arms to include both interventions and also a control arm, which was standard care without TXA. The numbers allocated to each arm were in the ratio 2:2:1. It was felt necessary to include the no TXA arm, control group 3, because although TXA is known to reduce blood loss, it was not the standard of care in our unit. However, it was stipulated in the protocol that there must be an interim analysis once 100 THA and 100 TKA patients had been recruited to decide on the continuation of the control group 3. At that time, 40 patients had been recruited into this group. Following this analysis, the DMEC recommended dropping control group 3, which was ratified by the TSC. This change was implemented following approvals from the sponsor, the research ethics committee and MHRA. This also resulted in a change in practice in our unit, with TXA being considered for all primary joint patients at the discretion of the anaesthetist.

The authors are aware of some limitations to this study. Firstly, it is a single-centre study; therefore, it could be argued that the results are not transferable to other centres due to different clinical practices. Secondly, randomisation is performed using sealed envelopes with tamper-proof labels instead of an automated system. While both systems were considered during the study design, it was decided that as it was a single-centre study with robust checks by the study site and by the NICTU, sealed envelopes were sufficient.

With TRAC-24, we intend to determine if the effect of TXA can be potentiated by continuing its administration post-operatively, at the time of greatest loss.

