**Methods/design:**

This is a phase IV, single-centred, open-label, parallel-group, randomised controlled trial. Participants are randomised to one of three groups: group 1, an intravenous (IV) bolus of TXA peri-operatively plus oral TXA post-operatively for 24 h; group 2, an IV bolus of TXA peri-operatively or group 3, standard care (no TXA). Eligible participants, including those with a history of thromboembolic disease, are allocated to these groups with a 2:2:1 allocation ratio. The primary outcome is the indirectly calculated blood loss 48 h after surgery. Researchers and patients are not blinded to the treatment; however, staff processing blood samples are. Originally 1166 participants were required to complete this study, 583 THA and 583 TKA. However, following an interim analysis after 100 THA and 100 TKA participants had been recruited to the study, the data monitoring ethics committee recommended stopping group 3 (standard care).

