**Fig. 2 Fig2:**
[figure not shown]
Schedule of enrolment, intervention and assessments. CRP C-reactive protein, Hb haemoglobin, Hct haematocrit, IV intravenous, INR International normalised ratio, KTS knife to skin, OHS Oxford hip score, OKS Oxford knee score, TXA tranexamic acid

When the study was initially planned, the peri-operative use of TXA was not a standard of care in primary THA and TKA in the UK and local site policy reserved its use for patients considered at high bleeding risk. Therefore, the no-intervention control group was deemed necessary to reflect current practice. However, following an interim analysis and review of safety data, which was performed as part of a scheduled data monitoring and ethics committee (DMEC) meeting, it was recommended that randomisation to control group 3 be discontinued. This DMEC meeting took place after 200 participants (40 of whom were in control group 3) had been recruited. By the time approval was gained for this protocol change, 134 participants had been recruited to the control group.

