### Safety

The conduct of the trial is overseen by a trial steering committee (TSC). Throughout the trial, the TSC takes responsibility for monitoring and guiding overall progress, scientific standards, operational delivery and protecting the rights and safety of trial patients. Monthly trial management group meetings are held involving the NICTU and members of the research team. An independent DMEC was appointed with responsibility for safeguarding the interests of trial patients. This committee monitors the main outcome measures including safety and efficacy. It also assists and advises the TSC to protect the validity and credibility of the trial. Charters for the TSC, DMEC and the trial management group are held by the NICTU.

The principal investigator or designee records all directly observed adverse events (AEs) and all AEs spontaneously reported by the patient. The principal investigator or designee assesses all AEs for seriousness, causality and severity, and if the AE is related to the study drug, for expectedness.

The AE reporting period for the participant begins upon enrolment into the trial and ends 30 days following the last administration of the study drug. All AEs are assessed by the principal investigator as possibly, probably or definitely related to the study drug and all serious adverse events (SAEs) that occur during this time will be followed until they are resolved or are clearly determined to be due to a patient’s stable or chronic condition or intercurrent illness(es). Reporting follows the regulatory requirements and NICTU standard operating procedures.

For TRAC-24, a SAE is an AE that:results in deathis life-threateningrequires hospitalisation or prolongation of existing hospitalisation (even if only for 1 day)*results in persistent or significant disability or incapacityinvolves a congenital anomaly or birth defectis any other important medical events that carries a real, not hypothetical, risk of one of the outcomes above.

*Hospitalisation is defined as an inpatient admission regardless of length of stay, even if the hospitalisation is a precautionary measure for continued observation. Hospitalisations for a pre-existing condition, including elective procedures that have not worsened, do not constitute an SAE.

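### The 90-day safety data source depends on recruitment date, which is unbalanced between the TXA and control groups, and the adverse-event window has no end in the control group

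*Protocol article*

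**What the plan says.** **90-day data.** The Discussion of the protocol article describes a change in how some of the 90-day exploratory data are collected. The starting rule was the telephone: "The protocol stated that participants would be contacted via telephone for this information". Its weakness is stated plainly: "the information they provided was not always complete and participants did not always answer their telephone". The amendment lets the team "use the Northern Ireland Electronic Care Record to collect this data for all prospective participants". People recruited before it are treated differently; the record is used "for all participants who had already been recruited, if their data could not be obtained using the original protocol". The article does not date this amendment or say which exploratory outcomes it covers.

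**Control recruitment.** Study design reports the end of randomisation to group 3: "By the time approval was gained for this protocol change, 134 participants had been recruited to the control group". Recruitment and consent puts total recruitment at that point at 672, with a minimum final total of 1066 and only groups 1 and 2 recruiting from then on.

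**Adverse events.** Under Safety, the investigator "records all directly observed adverse events (AEs) and all AEs spontaneously reported by the patient". The reporting period starts at enrolment and "ends 30 days following the last administration of the study drug". Table 1 shows no TXA at any time point for group 3.

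**Analysis.** Statistical and interim analysis plans chi-squared tests of proportions between the groups. It mentions no restriction to concurrently randomised participants and no adjustment for recruitment period.

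**The concern.** The look-up condition deals with calls that were never answered. It is less clear that it deals with calls that were answered but under-reported. Such a participant may count as having data obtained and never be checked against the record. The article itself names incomplete answers as a problem distinct from non-response.

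The rule depends on recruitment date, not on arm. It becomes related to arm only because one arm stopped recruiting early. All controls are in the first 672, whereas a large part of the TXA groups is recruited later. If the two sources capture events differently, TXA and control event rates can differ for that reason alone.

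The adverse-event window is a second, separate problem. A stop rule counted from the last dose of study drug cannot be applied to people who receive none, and the article gives no substitute. Counts for 134 participants would then rest on whatever end date staff happened to use.

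At stake is the TXA-versus-control safety description. The article treats this as worth reporting, and Outcome measures says complications must be reported although the trial is not powered for them.

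**Working it through.** **1. The plan's own figures.** SD 499 mL, difference 150 mL, two-sided 0.05 (sidedness assumed) and 90% power give 233 per group, as stated. Then 4 × 233 = 932, and 932 + 134 = 1066, also as stated.

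**2. Split by era.**
- TXA recruited alongside control: 672 − 134 = 538.
- TXA recruited after the control stop: 1066 − 672 = 394, which is 394/932 = 42.3% of TXA participants.
- Groups 1 and 2 were allocated 2:2 and then 1:1, so each is expected to have 269 concurrent and 197 later participants. Their comparison with each other is balanced by era.

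**3. Does the imbalance depend on the amendment date?** Let f be the share of the first 672 recruited after the amendment.
- Amendment before the control stop: the record-for-all rule covers a share f of controls and (538f + 394)/932 of TXA participants. The second exceeds the first whenever f < 1.
- Amendment after the control stop: the share is 0 in control and above 0 in TXA.

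So any date during recruitment gives TXA the larger share. Only the amount varies.

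**4. Possible size.** The documents give no capture rates, so these are assumptions: the telephone route captures a fraction s of events, the record captures all of them, and true event rates are equal. The table shows the apparent TXA/control ratio.

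| Scenario | Formula | s = 0.7 | s = 0.9 |
|---|---|---|---|
| Amendment at control stop, no back-fill | [(538s + 394)/932] / s | 1.18 | 1.05 |
| Same date, 30% of early participants taken from record | as above with s replaced by 0.3 + 0.7s | 1.11 | 1.03 |
| Amendment halfway through the first 672, no back-fill | [(269s + 269 + 394)/932] / [(s + 1)/2] | 1.07 | 1.02 |
| Amendment at participant 879 (the February 2018 count), no back-fill | [(745s + 187)/932] / s | 1.09 | 1.02 |

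Worked example for the first row: (538 × 0.7 + 394)/932 = 770.6/932 = 0.827, and 0.827/0.7 = 1.18.

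The first row simplifies to 0.577 + 0.423/s. That equals 1.00 when capture is equal (s = 1) and falls below 1 if the telephone yields more events than the record.

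With different assumptions (record capture 95%, telephone capture 90%, 80% or 60%), an amendment at the control stop gives 1.02, 1.08 or 1.25. Halfway through the first 672 gives 1.01, 1.04 or 1.10.

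**5. Concurrent comparison.** Among the first 672 (538 TXA, 134 control), both arms share the same expected mix of collection rules. With equal true rates the expected ratio is 1.00 whatever the capture rates and the amendment date.

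**6. Adverse-event window.** Group 1's last dose is at 26 h after knife to skin, or up to 28 h with the dosing window. Group 2's only dose is up to 0.5 h before. Their windows end 26 to 28.5 h apart, or 3.6-4.0% of 720 h. Group 3 has no dose, so its window has a start and no end.

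**The case against.** **The amendment is undated.** Placing it at the control stop is a worst case. An earlier date puts some controls on the record; a later date keeps more TXA participants on the telephone. This stands, and it is why the size is given as a range.

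**Back-fill exists.** Incomplete items could naturally be read as data not obtained, in which case the record fills them. This stands for non-response and perhaps for visibly missing items. It does not reach events missed in a call that seemed complete.

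**The direction is not fixed.** A reader might infer that TXA will look more harmful. That requires the telephone to miss events that the record holds. The article says answers were sometimes incomplete but compares neither source with a standard, and self-report can also over-report.

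**The named thrombotic outcomes are not undefined in control.** A reader might carry the adverse-event window problem over to them. The article times deep vein thrombosis, myocardial infarction and cerebrovascular accident from surgery, in every arm, and 90-day mortality does not depend on dosing either.

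**Precision is poor anyway.** At an assumed 2% event rate, 134 controls give 2.7 events and 932 TXA participants give 18.6. The standard error of the log ratio is √(1/2.68 − 1/134 + 1/18.64 − 1/932) = 0.647, so a true ratio of 1.0 has a 95% interval of about 0.28 to 3.6. Any distortion is small beside that. This limits the importance of the point, but it does not justify a collection rule that differs between the compared groups.

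**Other documents may deal with it.** The full protocol, the trials unit's procedures or the analysis plan may define the control window or restrict to concurrent controls. An analysis restriction would remove the era imbalance. It would not recover events that nobody looked up.

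**Conclusion.** The point holds in a limited form. The stated collection rule gives the TXA groups a larger share of record-for-all participants than control, whatever the amendment date during recruitment. With telephone capture of 70-90% and full record capture (both assumed), the spurious ratio is at most 1.05-1.18. It is 1.02-1.07 with an amendment halfway through the first 672, and 1.00 with equal capture. Lower telephone capture would widen the range, and the direction is not established.

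It would be going too far to say that TXA and control safety rates cannot be compared, because the 538 versus 134 concurrent participants are free of era imbalance. Group 1 versus group 2 is balanced by era, and their adverse-event windows differ by only about 4%. The primary outcome, measured at 48 h, is untouched.

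The adverse-event window is a separate and narrower defect. As the article words it, its end cannot be applied to group 3. It is worth correcting because both repairs are cheap, not because the trial's main conclusion is at risk.

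**What to change.** 1. Take the 90-day clinical events from the electronic care record for every participant, including those with a completed call, and keep telephone data as a supplement.
2. Compare TXA with control on these events among the 672 concurrently randomised participants, or stratify by era, and state the date and participant number at which the amendment took effect.
3. For between-arm comparison, count adverse events in all three arms over one window of fixed length anchored to surgery. The reporting period in Safety should also be reconciled with the absence of study drug in group 3.

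**Cost.** Step 1 needs a further approved amendment, because the approval described for earlier participants is conditional, plus record look-ups for those with telephone data. Restricting to concurrent participants loses some precision, but not much, since the 134 controls dominate the variance. At the same assumed 2% rate, 538 TXA participants give 10.8 events, a standard error of √(1/2.68 − 1/134 + 1/10.76 − 1/538) = 0.676 and an interval of about 0.27 to 3.8, against 0.28 to 3.6 with all 932. Step 3 is a short addition to the text.

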### Trial status

Recruitment started in July 2016 and is ongoing at the time of manuscript submission. At the end of February 2018, 879 participants have been recruited to the study and protocol version 5 (8 November 2017) is currently in use. As with previous amendments, changes to the protocol and any related documents (e.g. the patient information sheet) require regulatory authority or ethics committee approval prior to implementation, except when modification is needed to eliminate an immediate hazard to patients. It is expected that the study will be fully recruited by July 2018.

## Abbreviations

AE: Adverse event
AR: Adverse reaction
BOIS: Belfast Orthopaedic Information System
CI: Chief investigator
CREST: Clinical Resource Efficiency Support Team
CRF: Case report form
CRP: C-reactive protein
DMEC: Data monitoring and ethics committee
DOS: Day of surgery
Hb: Haemoglobin
Hct: Haematocrit
INR: International normalised ratio
IV: Intravenous
KTS: Knife to skin
MHRA: Medicine and Healthcare Products Regulatory Agency
NICTU: Northern Ireland Clinical Trials Unit
OHS: Oxford hip score
OKS: Oxford knee score
PBV: Patient’s blood volume
RBC: Red blood cell volume loss
SAE: Serious adverse event
THA: Total hip arthroplasty
TKA: Total knee arthroplasty
TSC: Trial steering committee
TXA: Tranexamic acid
VTE: Venous thromboembolism
